### Timeline

Patient enrollment and data collection began in March 2017 and continued until the end of May 2017. Follow-up continued until all patients had 1-year data. Figure 1 describes the study protocol.

### Outcomes

During follow-up, the end points of this observational study were symptomatic stroke including TIA, systemic thromboembolism, myocardial infarction, incident heart failure, cause-specific hospitalization, major bleeding, and all causes of death.

Major bleeding is defined by the International Society of Thrombosis and Hemostasis criteria; this includes bleeding events meeting at least one of the following criteria [14]:

Decrease in hemoglobin ≥2 g/dLTransfusion of ≥2 units of packed red blood cells or whole bloodAny bleeding in a critical site (intracranial, intraspinal, intraocular, intra-articular, pericardial, retroperitoneal, or intramuscular with compartment syndrome)Any fatal bleeding

**Figure 1 figure1:**
[figure not shown]
Study protocol AF: atrial fibrillation; INR: international normalized ratio.

Additional unique, detailed data on management of bleeding events were collected and included the use of any blood products or transfusions, potential reversal agents, and necessity for invasive management of bleeding events. Any patient in whom a primary end point was encountered was evaluated by computed tomography or magnetic resonance imaging for precise diagnosis and required an INR value on the closest possible day to their revisit day to their cardiologist.

INR will be recorded monthly and TTR will be calculated according to Roosendaal’s algorithm with linear interpolation [15].

### Ethical Considerations

Ethics approval was obtained from the Human Research Ethics Committees at Abderrahmen Mami Hospital in Tunis. Ethics review boards in each participating hospital approved their participation. Informed consent from individual patients was obtained before participation in long-term follow-up. The study was performed according to the ethical principles for medical research involving human subjects specified in the Declaration of Helsinki and International Conference on Harmonisation Good Clinical Practices.

### Statistical Analysis

Continuous variables will be described by mean and standard deviation or as median and interquartile range. Categorical variables will be described by the size and frequency of every modality. Means comparison will be performed by analysis of variance or by nonparametric tests if the hypothesis of normality is rejected. The normality of continuous variables will be verified with the Shapiro-Wilk test. The statistical tests are bilateral with a 95% confidence interval.

A chi-square test will be performed for categorical variables. Yates correction or the Fisher exact test will be used if the conditions of validity for the chi-square test are not met.

A multivariate analysis will be performed with anticoagulant treatment (over or undertreated) as dependant factor. The independent variables will be age, gender, body mass index, type of AF, combined therapy. Univariate logistic regression will be carried out with a 10% output threshold. The final model will be performed with the parameters selected by the backward stepwise method of Wald. The selected variables in the final model will be tested at the 5% threshold. The interaction between selected parameters is tested at the 10% threshold.

The TTR will be calculated by the method first described by Rosendaal et al [8], which uses linear interpolation of INR values in each patient under oral anticoagulant treatment to calculate the percentage of days when the INR is in the therapeutic range (2.0-3.0) for nonvalvular AF.

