### Sample Size and Data Collection

A minimum of 10 consecutive patients per cardiologist were enrolled with a target of 1800 patients for NATURE-AF. A total of 186 cardiologists agreed to participate.

While it was anticipated that most investigators would be hospital-based cardiologists, recruitment by office-based cardiologists was allowed if follow-up of patients was deemed feasible.

The plan was to have 1 baseline visit and 1 visit every 3 months over a 1-year period. Enrollment into the registry started March 1, 2017, with an inclusion period estimated up to 3 months. All patients were followed for 12 months. During this period, all participants revisited their cardiologists at the usual intervals (3 months), and patients taking oral anticoagulant therapy consult (or visited) at least once every month for INR to be measured.

The data collected were managed by the Clinical Suite platform (Dacima Software), which complies with international standards including US Food and Drug Administration 21 Code of Federal Regulations Part 11, US Health Insurance Portability and Accountability Act, International Conference on Harmonisation, and Medical Dictionary for Regulatory Activities. The Clinical Suite platform allowed us to track the data entered, check for inconsistencies and missing data, and schedule monitoring visits. A steering committee was set up to monitor patient inclusions, verify data sources, perform the audit trail, and prepare the statistical analysis plan for the study. Data were collected every 3 months regardless of patient clinic follow-up. All incident events and therapeutic changes were entered at each collection interval.

Baseline data included patient demographics, medical history, cardiovascular history, details of AF history and therapies, vital signs, laboratory measurements, electrocardiographic data, cardiac imaging parameters, details of medical management, and any contraindications to anticoagulation. At follow-up, major incident events and procedures, subsequent vital signs, laboratory studies, imaging parameters, and medication changes were recorded, and the daily acenocoumarol (Sintrom) dose and INR value were noted for all patients taking acenocoumarol. In-depth data regarding antithrombotic therapies, dosing, discontinuations, and reasons for discontinuations were included in follow-up medication data.

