## Results

About 95 cardiologists included 918 patients in the registry with a 1-year follow-up period. All patients provided written informed consent. Patients were officially enrolled in NATURE-AF only if they were aged 20 years and older and had had at least 1 episode of AF recorded on a standard 12-lead electrocardiogram or on 24-hour Holter monitor.

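### Patients are recruited in groups of about ten per cardiologist but analysed as independent, so intervals for overall estimates and tests of factors that differ between cardiologists are too optimistic

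*Protocol article*

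**What the plan says.** Recruitment is organised by cardiologist. The section Sample Size and Data Collection states: "A minimum of 10 consecutive patients per cardiologist were enrolled with a target of 1800 patients for NATURE-AF". It adds: "A total of 186 cardiologists agreed to participate". The Results section reports what was achieved: "About 95 cardiologists included 918 patients in the registry with a 1-year follow-up period".

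The Statistical Analysis section sets out the methods. On continuous variables: "Means comparison will be performed by analysis of variance or by nonparametric tests if the hypothesis of normality is rejected". Categorical variables get a chi-square test, with Yates correction or Fisher's exact test as fallback. A logistic regression takes over- or undertreatment with anticoagulant as outcome, and age, gender, body mass index, type of AF and combined therapy as covariates. It uses a 10% univariate screen and backward Wald selection, and then: "The selected variables in the final model will be tested at the 5% threshold". On sidedness and confidence level: "The statistical tests are bilateral with a 95% confidence interval".

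The article mentions no cardiologist, centre or region term, random effect, robust variance or design effect. It assigns a statistical analysis plan to the steering committee; that plan is not shown.

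**The concern.** The named methods, in their standard form, take each patient as an independent observation. The design delivers groups of consecutive patients from the same doctor. The outcome of the regression is largely that doctor's decision, so the patients of one cardiologist plausibly resemble each other more than patients of different cardiologists. If they do, 918 patients carry less information about national practice than 918 independent patients would.

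The frequency and quality of anticoagulation and the event incidences are the registry's headline results. If their precision is overstated, differences from other registries, or between groups that follow cardiologist lines, can look firmer than they are.

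**Working it through.** **Inputs.** From the article: 186 cardiologists and 1800 patients planned; about 95 cardiologists and 918 patients achieved; two-sided, 95%, 5%. Assumed, because the article gives no value: ICC from 0.01 to 0.20.

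**The plan's own figure.** The target of 1800 comes with no power, precision or design effect, so there is no statistical calculation to reproduce. The only arithmetic to hand is cardiologists times the minimum: 186 × 10 = 1860, close to but not equal to 1800.

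**Cluster size.** Planned 1800/186 = 9.68; achieved 918/95 = 9.66. Taking 95 as exact, the achieved mean is below the stated minimum of 10, so at least one cardiologist enrolled fewer than 10.

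**Overall estimates.** With m = 9.66 and N = 918:

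- design effect DE = 1 + (m − 1) × ICC
- effective sample size = N/DE
- true coverage of a naive 95% interval = 2Φ(1.96/√DE) − 1
- correct half-width = 1.96 × √(p(1 − p) × DE/N), shown for illustrative p = 50% and p = 5%

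| ICC | DE | Effective n | Coverage | Half-width, p = 50% | Half-width, p = 5% |
|---|---|---|---|---|---|
| 0 | 1.00 | 918 | 95.0% | 3.23 points | 1.41 points |
| 0.01 | 1.09 | 845 | 94.0% | 3.37 | 1.47 |
| 0.02 | 1.17 | 782 | 93.0% | 3.50 | 1.53 |
| 0.05 | 1.43 | 641 | 89.8% | 3.87 | 1.69 |
| 0.10 | 1.87 | 492 | 84.9% | 4.42 | 1.93 |
| 0.20 | 2.73 | 336 | 76.4% | 5.35 | 2.33 |

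Example: at ICC 0.05, DE = 1 + 8.66 × 0.05 = 1.43, √1.43 = 1.20, and 2Φ(1.96/1.20) − 1 is about 0.90.

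**Unequal clusters.** With DE = 1 + ((1 + CV²)m − 1) × ICC and an assumed coefficient of variation of cluster size of 0.5, DE is 1.55 at ICC 0.05 (coverage 88.4%) and 2.11 at ICC 0.10 (82.3%).

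**Planned size.** At 1800 patients over 186 cardiologists the design effects are the same. The effective sample sizes are 1255 (ICC 0.05) and 964 (ICC 0.10). The problem therefore does not come from under-recruitment.

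**TTR.** Only patients under oral anticoagulant treatment with INR values contribute. Clusters are smaller, and the design effect is below the tabulated one at the same ICC.

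**Regression.** Data were simulated with a cardiologist random intercept (95 clusters of 10, 1500 replicates per cell, no true covariate effect) and analysed by ordinary logistic regression. The rejection rate at nominal 5% was:

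| Share of covariate variance between cardiologists | Outcome ICC 0.05 | 0.10 | 0.20 |
|---|---|---|---|
| 0 | 3.9% | 5.1% | 5.0% |
| 0.05 | 5.3% | 5.0% | 5.4% |
| 0.10 | 4.6% | 5.3% | 7.0% |
| 0.30 | 5.2% | 7.4% | 8.1% |
| 1 (a cardiologist-level factor) | 9.7% | 12.5% | 18.4% |

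The simulation error is about √(0.05 × 0.95/1500) = 0.6 points. The outcome ICC here is on the logit scale, which helps to explain why the last row lies below one minus the coverage in the first table.

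**The case against.** The strongest reply is that the article condenses a fuller plan, and that the choice of variance estimator is commonly left to the analysis plan, which is not shown and may deal with clustering. This limits the point to the methods as the article states them. It does not dispose of it: the section goes as far as naming the tests, covariates, selection method and thresholds, and that specification does not fit the recruitment design.

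Three further objections stand in part or in full.

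- The section describes variables by means, medians and frequencies, and its reference to 95% sits in a sentence about tests. It does not expressly plan an interval for each overall figure. The coverage results apply to any such interval that is reported.
- All five regression covariates are patient-level. None is a cardiologist, practice or region factor.
- The ICC is unknown. At 0.01 or 0.02 the effect is small.

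A reader might infer more than the article supports:

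- That every 5% test is inflated. The simulation shows otherwise for covariates that vary within a cardiologist's patients.
- That comparisons of regions, or of hospital with office practice, are faulty. The section plans none. They would be affected if made.
- That the target of 1800 is wrong. It rests on no stated precision or power.
- That clustering turns prescriber habits into false patient-level predictors. That is confounding by prescriber, a separate matter from understated variance, and cluster-robust errors would not remove it.

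**Conclusion.** The point holds in a limited form and should be acted on. Followed as written, the Statistical Analysis section ignores grouping by cardiologist. This makes 95% intervals around overall proportions, incidences and mean TTR too narrow, and tests of factors that differ between cardiologists too liberal, whenever the ICC is positive.

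The size depends on an ICC that the article does not give: negligible near 0.01, material at 0.05, serious at 0.10 and above. For age, gender and body mass index, which plausibly vary mostly within a cardiologist's patients, the 5% tests are about right. For combined therapy or type of AF, which may cluster, modest inflation to about 8% is possible. The figures assume equal cluster sizes unless noted, and the ICC need not be the same for prescribing, events and TTR.

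**What to change.** In the Statistical Analysis section, and in the analysis plan, state that:

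- confidence intervals and group comparisons use cluster-robust (sandwich or GEE) variance with the enrolling cardiologist as cluster;
- the logistic regression uses a cardiologist random intercept or cluster-robust errors, and the same standard errors drive the univariate screen, the backward Wald selection and the interaction tests;
- the ICC is reported for the main outcomes.

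The choice between the two regression options should be made in advance. A random intercept gives odds ratios conditional on the cardiologist; robust errors leave the ordinary odds ratios unchanged and correct only their precision. Adding region or practice type as fixed effects is a matter of preference and is not needed to correct this error.

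The cost is a change of wording and somewhat wider intervals. No new data should be needed, provided that the enrolling cardiologist is recorded for each patient; recruitment by cardiologist makes this likely, but the article does not say so. If the ICC proves trivial, the results will hardly change.

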**Methods:**

A total of 1800 consecutive patients with AF by electrocardiogram, reflecting all populations of all geographical regions of Tunisia, will be included in the study, with the objective of describing the epidemiological pattern of AF. Patients will be officially enrolled in the National Tunisian Registry of Atrial Fibrillation (NATURE-AF) only if an electrocardiogram diagnosis (12-lead, 24-hour Holter, or other electrocardiographic documentation) confirming AF is made. The qualifying episode of AF should have occurred within the last year, and patients do not need to be in AF at the time of enrollment. Patients will be followed for 1 year. Incidence of stroke or transient ischemic attack, thromboembolic events, and cardiovascular death will be recorded as the primary end point, and hemorrhagic accidents, measurement of international normalized ratio, and time in therapeutic range will be recorded as secondary end points.

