Demographic and prognostic AF data from other ethnic groups would not be generalizable to our population. Thus, a register or a survey dealing with the demographic and prognostic characteristics of AF in Tunisia is essential, making it possible to identify its specific characteristics inherent in part to ethnic particularities but especially to particularities of the local health system.

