### Registry Objectives

The National Tunisian Registry of Atrial Fibrillation (NATURE-AF) is a prospective observational accumulation of data used in the investigation of the optimal intensity of anticoagulation in Tunisian AF patients and present status of anticoagulation treatment in Tunisia.

The primary end point of NATURE-AF is to describe the incidence of stroke or transient ischemic attack (TIA), thromboembolic event, and cardiovascular death every 3 months up to 1 year.

The secondary end points are as follows:

Hemorrhagic accidents, every 3 months up to 1 yearInternational normalized ratio (INR) every month for 1 yearMean time in therapeutic range (TTR) obtained in patients who receive anticoagulant therapy

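### The only multivariable model has no care-setting or region term, so it cannot show whether over- or undertreatment varies by setting or region within Tunisia

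*Protocol article*

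**What the plan says.** All references are to the protocol article.

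- **Background (Introduction)** says that a Tunisian registry makes it possible to "identify its specific characteristics inherent in part to ethnic particularities but especially to particularities of the local health system".
- **Registry Objectives** is narrower. The data are "used in the investigation of the optimal intensity of anticoagulation in Tunisian AF patients and present status of anticoagulation treatment in Tunisia", and the end points are event incidence, bleeding, INR and time in therapeutic range.
- **Abstract, Methods** describes the sample as "reflecting all populations of all geographical regions of Tunisia". **Study Design and Patient Enrollment** takes both in- and outpatients. **Sample Size and Data Collection** expected that "most investigators would be hospital-based cardiologists, recruitment by office-based cardiologists was allowed" where follow-up was feasible.
- **Statistical Analysis** gives one multivariable model: "A multivariate analysis will be performed with anticoagulant treatment (over or undertreated) as dependant factor". Its candidates are fixed: "The independent variables will be age, gender, body mass index, type of AF, combined therapy". Selection is a univariate screen at 10%, and then "The final model will be performed with the parameters selected by the backward stepwise method of Wald", with a 5% threshold in the final model.
- **Results** reports 918 patients from about 95 cardiologists.

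**The concern.** The design builds in variation in where and by whom patients are treated, and the rationale gives the health system more weight than ethnicity. Yet the only adjusted analysis uses none of that variation. Four of its five predictors describe the patient or the arrhythmia, and the fifth, combined therapy, is a treatment choice.

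Two things are at stake. First, the model cannot say whether over- or undertreatment differs between hospital and office cardiologists or between regions. For a registry on the status of anticoagulation in one country, that is the most direct system-level question its own data can address. Second, if setting or region is related both to a listed predictor and to mis-treatment, that predictor's odds ratio will absorb part of the difference, and a reader may take it for a patient characteristic.

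**Working it through.** **1. Set the text side by side.** Multivariable models described: 1. Candidate predictors: 5. Setting, region or site terms among them: 0. The analysis of variance, nonparametric and chi-square comparisons in the same section name no grouping variable, so no stated analysis supplies the missing terms. The article states no figure on this point that could be reproduced.

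**2. How far could omitting setting move an odds ratio?** The article gives no data on how setting relates to age, AF type or treatment, so this is illustration only.

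Assumed inputs: risk of mis-treatment 0.40 in office patients; hospital share 50% in patients without the predictor and *s* in patients with it; true odds ratio of the predictor 1.00; setting odds ratio (hospital vs office) *k*.

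- Hospital odds = *k* × 0.40/0.60.
- Risk in each predictor group = share × hospital risk + (1 − share) × 0.40.
- The odds ratio without setting is the ratio of the two groups' odds.

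Example with *k* = 2 and *s* = 70%:

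- hospital odds 1.333, risk 0.571
- without the predictor: 0.5 × 0.571 + 0.5 × 0.40 = 0.486
- with the predictor: 0.7 × 0.571 + 0.3 × 0.40 = 0.520
- odds ratio = (0.520/0.480)/(0.486/0.514) = 1.15

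| Hospital share with predictor | *k* = 1 | *k* = 1.5 | *k* = 2 | *k* = 3 |
|---|---|---|---|---|
| 50% | 1.00 | 1.00 | 1.00 | 1.00 |
| 60% | 1.00 | 1.04 | 1.07 | 1.11 |
| 70% | 1.00 | 1.08 | 1.15 | 1.24 |
| 80% | 1.00 | 1.13 | 1.23 | 1.39 |

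The first row and first column show no shift: setting must be related to both the predictor and the outcome.

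**3. The direction is also unknown.** Take a second set of assumptions: 70% hospital patients; 45% of hospital and 25% of office patients older; office risk 0.40; no true age effect.

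- Hospital share among older patients = 0.315/(0.315 + 0.075) = 0.808.
- Hospital share among younger patients = 0.385/(0.385 + 0.225) = 0.631.
- If offices have twice the odds of mis-treatment, hospital risk is 0.25. The age groups then have risks 0.279 and 0.305, and the age odds ratio is 0.88. For office-vs-hospital odds ratios of 1.5, 3 and 4 it is 0.93, 0.81 and 0.76.
- If hospitals have twice the odds, hospital risk is 0.571. The risks are then 0.538 and 0.508, and the age odds ratio is (0.538/0.462)/(0.508/0.492) = 1.13.

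**4. Can the data carry the extra terms?** Setting and region, as defined by the recruiting cardiologist, are constant within a cardiologist, so clustering bears on them fully. Mean cluster size is 918/95 = 9.66. The design effect is 1 + (9.66 − 1) × ICC, with the ICC assumed.

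I take 20% mis-treated, over and under together, as the assumed low end, and 14 degrees of freedom as the assumed upper end. The 14 are 7 for the listed predictors with AF type in four classes, 1 for setting, and 6 for seven regions.

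| ICC | Design effect | Effective N | Effective outcomes at 20% | Per df at 14 df |
|---|---|---|---|---|
| 0 | 1.00 | 918 | 184 | 13.1 |
| 0.01 | 1.09 | 845 | 169 | 12.1 |
| 0.05 | 1.43 | 641 | 128 | 9.2 |
| 0.10 | 1.87 | 492 | 98 | 7.0 |
| 0.20 | 2.73 | 336 | 67 | 4.8 |

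If clustering is ignored, the support for the new terms looks better than it is. With three regions (2 df) and AF type in three classes, the total is 6 + 1 + 2 = 9 df, and at ICC 0.10 there are 98/9 = 10.9 effective outcomes per df. That is the case for coarse grouping of region.

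**The case against.** **The health-system phrase is rationale, not an objective.** This stands. It appears in the Introduction, and neither the objectives nor the end points promise attribution to the health system. A reader might infer that the registry fails a stated objective; the article does not support that.

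**All patients are in Tunisia.** This stands. Setting and region can show variation inside the country only. What is particular to the national system needs comparison with other countries, which the Discussion mentions without a method. So it would be wrong to present the added odds ratios as answering the Background statement.

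**Confounding is not shown.** This stands. A reader might infer that the age and AF-type odds ratios are confounded by care setting. Nothing in the article shows that setting is related to either predictor or to mis-treatment. Setting may also lie downstream of age, if older patients are sent to hospital. Adjustment would then remove part of the total age association rather than a bias. This is why both versions of the model should be reported.

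**The statistical analysis plan or the unnamed comparisons may cover it.** This stands only in part. Unadjusted comparisons by setting or region are neither stated nor excluded, and a plan was to be prepared. But the article does not defer the covariates of this model: it lists them. A plan that follows the article inherits the gap.

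**The variables may not be recorded.** The baseline data list names no setting or region field. Both should be derivable from the recruiting cardiologist, but that is an inference to confirm.

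**Conclusion.** The point holds in limited form. The model's closed list of five predictors has no setting or region term, so it cannot show whether over- or undertreatment varies along either line within Tunisia. This follows from the text and needs no assumption.

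That the listed predictors' odds ratios may partly reflect such differences is a possibility, not a finding. Under the assumed inputs above, a true odds ratio of 1.00 would appear as anything from 1.00 to 1.39, or as low as 0.76 if offices have the higher odds of mis-treatment. The shift is zero if setting is unrelated to either the predictor or the outcome.

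The change is worth making because it is cheap and concerns an analysis the article fixes explicitly. The descriptive end points do not depend on it.

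**What to change.** In Statistical Analysis:

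1. Add care setting (hospital vs office-based cardiologist) and region of the recruiting site to the over-/undertreatment model. Retain both regardless of the 10% screen and the backward Wald selection, which could otherwise drop them.
2. Handle clustering by cardiologist with robust standard errors or a random intercept.
3. Report the model with and without the two terms, so that readers can see how far the age, AF-type and other odds ratios move.
4. Present the setting and region odds ratios as within-country variation in anticoagulation practice, not as the effect of the national health system, and describe the other odds ratios as associations.

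The cost is a short amendment to the analysis section, confirmation that setting and region can be assigned for each of the roughly 95 cardiologists, a few degrees of freedom, and somewhat wider intervals. Region may need to be grouped coarsely, and the grouping should be fixed before the model is fitted. No new patient data should be needed if the assignment can be made from the recruiting site.

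### Data-driven selection among five predictors already named overstates weak odds ratios or, if effects are strong, invites chance interactions; one fixed model avoids both

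*Protocol article*

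**What the plan says.** All of this stands in the Statistical Analysis section of the protocol article.

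- Outcome: "A multivariate analysis will be performed with anticoagulant treatment (over or undertreated) as dependant factor".
- Candidate predictors, fixed in advance: "The independent variables will be age, gender, body mass index, type of AF, combined therapy".
- First filter: "Univariate logistic regression will be carried out with a 10% output threshold".
- Second filter: "The final model will be performed with the parameters selected by the backward stepwise method of Wald". No separate removal threshold is given.
- Test of the survivors: "The selected variables in the final model will be tested at the 5% threshold".
- Interactions: "The interaction between selected parameters is tested at the 10% threshold". None is named, and the article does not say whether every pair is tested.
- General rule: "The statistical tests are bilateral with a 95% confidence interval".

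The article describes no full-model report and no correction for selection.

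**The concern.** Selection is usually justified by too many candidates for the data. Here the list has only five entries and was chosen beforehand. Passing it through two significance filters means that an odds ratio reaches the table only when chance has made it large enough. The ordinary Wald interval is then reported as though the surviving model had been fixed from the start. The interaction step adds up to ten further tests at a lenient level, with no hypothesis named.

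At stake is the one multivariable model in the article, which would say which patients are over- or undertreated. Readers could be given overstated associations, or interactions that arose by chance, depending on how strong the true effects are.

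**Working it through.** The article gives no event count, power or precision for this model, so there is no figure of its own to reproduce. Three checks follow.

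**1. Is selection needed?** Inputs: 918 patients enrolled (Results section), a target of 1800 (Sample Size and Data Collection section) and five predictors. Outcome prevalence is not given; 10-50% is assumed. Outcomes per predictor = N × prevalence / 5.

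- N = 918: 918 × 0.10 / 5 = 18.4, up to 918 × 0.50 / 5 = 91.8.
- N = 1800: 1800 × 0.10 / 5 = 36, up to 1800 × 0.50 / 5 = 180.

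A type-of-AF variable with more than two categories adds terms. With seven terms in all (assumed), the low end is 918 × 0.10 / 7 = 13.1. The counts assume that all enrolled patients enter the model and fall in proportion if only a subset does.

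**2. What does selection do to the estimates?** The procedure was simulated: univariate p<0.10, then backward Wald removal at 5% or 10%. It was compared with one model holding all five predictors. Assumptions not in the article: two continuous and three binary predictors, latent correlation 0.2, true odds ratios 1.15, 1.20, 1.00, 1.50 and 1.30; 800-1500 runs per setting.

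Each cell shows the mean odds ratio when retained, then its excess on the log scale and the coverage of the nominal 95% interval. Excess = ln(mean retained OR) / ln(true OR) − 1; for example, ln 1.47 / ln 1.20 − 1 = 0.3853 / 0.1823 − 1 = 1.11.

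| Setting (N, prevalence, removal) | True 1.15 | True 1.20 | True 1.30 | True 1.50 | Null, if kept: coverage |
|---|---|---|---|---|---|
| 918, 30%, 5% | 1.24 (54%; 89%) | 1.47 (111%; 87%) | 1.61 (82%; 90%) | 1.62 (19%; 95%) | 0% |
| 918, 30%, 10% | 1.22 (42%; 94%) | 1.42 (92%; 92%) | 1.54 (65%; 92%) | 1.58 (13%; 96%) | 44% |
| 918, 15%, 5% | 1.29 (82%; 89%) | 1.63 (168%; 81%) | 1.74 (111%; 88%) | 1.75 (38%; 94%) | 0% |
| 1800, 30%, 5% | 1.18 (18%; 94%) | 1.33 (56%; 93%) | 1.43 (36%; 93%) | 1.53 (5%; 96%) | 0% |

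- The null predictor was kept in about 3-7% of runs. Its 0% coverage at 5% removal is a matter of logic: a Wald p below 0.05 means that the 95% interval excludes 1.
- With every true odds ratio at 2.0 (N = 918), retained estimates averaged 2.00-2.04 and coverage was 95-99%.
- The full five-predictor model recovered the true values and covered 93-96% in every setting.
- Standard errors after selection were only 0-4% smaller than in the full model. The under-coverage comes from estimates shifted by selection, not from visibly shorter intervals.

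Further runs on a per-SD scale (N = 918, 30% prevalence, correlation 0.2, 5% removal) agree. A true log odds ratio of 0.15 averaged about 0.22 when retained (0.22 / 0.15 − 1 = 47%). A true 0.10 averaged about 0.20 (100%), with 87% coverage.

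**3. How often does a false interaction appear?** If k predictors survive and all pairs are tested, there are m = k(k − 1)/2 tests. Treating them as independent, the chance of at least one false positive is 1 − 0.9^m.

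| k kept | m pairs | 1 − 0.9^m |
|---|---|---|
| 2 | 1 | 10% |
| 3 | 3 | 27% |
| 4 | 6 | 47% |
| 5 | 10 | 65% |

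Simulation shows which row applies (N = 918, 30% prevalence, 5% removal):

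- Weak effects (log odds ratios 0 to 0.15 per SD): on average 1.7 predictors kept, and a false interaction in 7-8% of runs.
- Intermediate effects (0, 0.2, 0.2, 0.3, 0.3): 37% of runs, with 6-20% inflation and 95-97% coverage for the non-null predictors.
- Strong effects: 63-64% of runs, with 1-8% inflation and 95-98% coverage.

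**The case against.** The best counter-arguments concern size and consequence.

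- **The two harms largely exclude each other.** Inflation needs weak effects, and then few predictors survive to be paired. Frequent false interactions need most predictors to survive, and then inflation nearly vanishes. This stands. A reader might infer that the registry would report overstated odds ratios and probable chance interactions together, but no single simulated setting shows both at full size.
- **The magnitudes rest on assumptions.** Prevalence, effect sizes, correlation and removal threshold are absent from the article, and pairwise testing is an inference. This stands. With 10% removal, coverage for weak effects at N = 918 is 92-94%, and at N = 1800 it is close to nominal. The direction of the bias does not depend on these choices.
- **Too-narrow intervals.** A reader might infer that selection shortens the intervals materially. With standard errors at most about 4% smaller, that is not supported; the fault is that the intervals ignore selection.
- **Lost confounders.** A reader might infer that univariate screening discards important confounders. The article names no exposure whose effect is to be adjusted, so this is not pursued.
- **Low consequence.** The Registry Objectives section lists incidence as the primary end point, and bleeding, INR and TTR as secondary. This model is in neither list, which limits the weight of the point.
- **The unseen analysis plan may add a full-model table or an exploratory label.** Possibly, but the article itself commits to the selection procedure, so this is a stated method and not an omitted detail.
- **The outcome joins two opposite states.** It needs a definition before any odds ratio from this model can be read. That is true, but it is a separate matter that applies equally to both approaches.

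**Conclusion.** The point holds in a limited form. Selection among five pre-named predictors is unnecessary at 918 patients for an assumed prevalence of 10-50%, and it does harm in one of two ways.

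- **Weak true effects:** retained log odds ratios are overstated by roughly 45-100% for true values of 0.10-0.15 per SD, and by more for weaker ones. Nominal 95% intervals cover about 81-94% for such effects, less for near-null ones, and about 0-45% for null predictors kept by chance, depending on the removal threshold.
- **Strong true effects:** inflation is negligible, but if all pairs are tested the chance of at least one false interaction is about 35-65%.

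These are assumption-dependent ranges, not predictions for this registry. They concern a secondary explanatory model; a reader should not infer that the incidence estimates for the primary end point are affected. The change is worth making because it costs almost nothing, not because a main result is at risk.

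**What to change.** State in the analysis plan that age, gender, body mass index, type of AF and combined therapy enter one logistic model together, without univariate screening or stepwise elimination. Fix the functional form for age and body mass index in advance, so that it does not become a new data-driven choice. Report every odds ratio with its 95% CI, whether or not it is significant. Drop the general interaction search, or replace it with one or two interactions named beforehand and labelled exploratory.

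This changes wording only and needs no new data. The downside is a table that keeps non-significant predictors.
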